**Reasons for admission**		
Symptoms	718 (81.0)	116 (87.9)
Acute coronary event	97 (10.9)	15 (11.4)
Elective procedure	26 (2.9)	0 (0.0)
Atrial fibrillation	10 (1.1)	1 (0.8)
Other	6 (0.7)	0 (0.0)
Unknown	30 (3.4)	0 (0.0)

Data are *n* (%). Age is available for 883 screened patients.

#### Study measures

##### Visit schedule

This is a longitudinal study with two follow-up points. Data (Table 2) are collected at baseline (during the hospital admission), then at three and six months following randomization, plus or minus two weeks. Follow-up data are collected by email, post and telephone, or during a home visit if required. Recommended techniques, such as enclosing stamped, addressed envelopes for returning questionnaires and sending reminders, will be used to maximize response rates [18].

**Table 2 T2:** Data collection schedule

**Variable**	**Measurement tool**	**Time-point**				**Type of administration**
		**Screening**	**Baseline**	**3 months**	**6 months**	
Age	Demographics	×				Audit
Sex	Demographics	×				Audit
Postcode	Demographics	×				Audit
Health-related quality of life	EQ-5D		×	×	×	Posted questionnaire
Mood	Clinical Outcomes in Routine Evaluation (10-item version)		×	×	×	Posted questionnaire
Satisfaction	Social Satisfaction Questionnaire		×	×	×	Posted questionnaire
Costs	Valuing Health Change Questionnaire		×	×	×	Posted questionnaire
Uptake	Qualitative			×	×	Interview
Adherence	Qualitative			×	×	Interview
Smoking status	Qualitative		×	×	×	Interview
Alcohol consumption	Qualitative		×	×	×	Interview
Diet	Qualitative		×	×	×	Interview
Physical activity	Qualitative		×	×	×	Interview

*EQ-5D*, European Quality of Life - 5 Dimensions.

##### Assessment tools

Change in lifestyle will be determined by self-reported changes in alcohol consumption [19], smoking, diet and physical activity. Social satisfaction will be measured using the Social Satisfaction Questionnaire, a validated eight-item scale found to be a suitable outcome measure in people with substance use disorders [20]. Subjective wellbeing, psychological problems and functioning will be measured using the Clinical Outcomes in Routine Evaluation (10-item version). [21]. Health-related quality of life will be assessed using the European Quality of Life - 5 Dimensions (EQ-5D) [22]. The EQ-5D is a generic measure of health status, where health is characterized on five dimensions (mobility, self-care, ability to undertake usual activities, pain, anxiety or depression). The EQ-5D visual analogue scale will also be completed. The EQ-5D has been validated in the UK.

#### Health economics

Patients will also complete a questionnaire developed specifically for the trial as part of the incentives sub-study. The Valuing Health Change Questionnaire asks about the perceived difficulty in changing health behaviour, willingness to accept financial (dis)incentives (and minimum acceptable incentive amounts) and some supplementary questions required for the analysis in order to analyze the incentive, including attitudinal and time preference questions.

#### Qualitative data

There are no suitable quantitative measures of uptake, participation and maintenance of behaviour change. Information about participants’ acceptance of lifestyle advice, motivation to change and experience of effecting change will therefore be collected using qualitative methods in a structured interview, which will be conducted at the three and six-month follow-up points. Interviews will be conducted face-to-face or by telephone. The primary endpoints for the trial will be coded from this information and analyzed quantitatively. The interview data will be analyzed using a thematic framework approach and will be used to inform the development of a larger-scale trial.

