**Methods and design:**

This is a single-centre, randomized, unblinded feasibility trial in an acute hospital setting which aims to assess the feasibility of a definitive trial and provide proof of concept for the systematic delivery of individualized lifestyle advice in patients managed through an acute cardiology in-patient service.

Patients will be recruited before discharge and randomized to two groups. A control group will receive the usual lifestyle assessment and referral, while an intervention group will receive the usual assessment plus the new individualized lifestyle assessment and referral. The new assessment will inform assignment of each patient to one of three categories based on personal barriers to change. Patients may be referred to a formal lifestyle-change programme, through the ‘Leeds Let’s Change’ website, or they may be guided in self-management, using goal setting, or they may be assigned to a ‘deferment’ category, for reassessment at follow-up. These latter patients will be given a contact card for the ‘Leeds Let’s Change’ service.

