### Trial design

The study is designed as a single-centre, randomized, unblinded feasibility trial in an acute hospital setting (Figure 1).

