### Study conditions

Participants are randomized, using block randomization with randomly varying block sizes, in equal proportions, with no stratification, to receive either usual lifestyle assessment or an enhanced lifestyle assessment using an automated 24-hour telephone randomization service provided by the clinical trials research unit. The usual lifestyle assessment comprises a series of questions that identify lifestyle factors (that is, smoking habits, alcohol consumption, physical activity and weight) that contribute to an increased risk of vascular events. The enhanced lifestyle assessment includes the usual assessment but also contains an evidence-based lifestyle referral assessment based on factors that predict change [2,4]. The aim of this enhanced assessment is to aid healthcare professionals in directing patients toward appropriate lifestyle-change interventions. The assessments are delivered in the hospital ward by research staff before discharge.

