#### Statistical analysis

The primary analysis will be conducted on the intention-to-treat sample, including all randomized participants in the groups to which they were randomized. Analysis will focus on descriptive statistics and confidence interval estimation rather than formal hypothesis testing. The primary outcome of successful uptake of lifestyle advice is made up of two components: accepting referral or self-referral and participation in lifestyle interventions or self-management. The first is a binary outcome (yes, no) while the second is ordinal (none, initiated, persisted and maintained). Both will be summarized in each group, along with 95% confidence intervals to provide evidence of proof of concept.

A standard CONSORT-approved diagram will depict the flow of patients through the study from screening to analysis (see Figure 3 for enrolment to allocation stages only). This diagram summarizes the feasible eligible, recruitment and refusal rates. It will also summarize the 3- and 6-month follow-up rates. The distributions of the data at baseline, and at 3 and 6 months after randomization will be explored, with unusual values noted and explained. Baseline variables will be summarized as *n* (%), mean (standard deviation) or median (interquartile range), as appropriate, both overall and by randomized group, to characterize the sample and look for any imbalances. Risk factors for vascular events will be summarized, together with the frequency at which patients seek help. Referral choice will then be summarized by randomized group. Responses to the new assessment will be explored, including any changes between first and second assessments. Protocol violations will be reported, including an exploration of the predictors of any missing data. The primary outcomes will be summarized descriptively by behaviour change in relation to risk factors and by health-related quality of life, mood and social satisfaction to assess the relationship between the process and the clinical endpoints. Completion rates and missing item data will be summarized for key secondary outcomes, together with estimates and variances to aid calculation of sample size for a definitive trial.

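### Primary endpoints are coded from self-report interviews in an unblinded trial with no masking of the coding described, and the follow-up reassessment of deferred intervention patients is not placed in the schedule or ordered relative to the outcome questions

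*Protocol article*

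**What the plan says.** Trial design describes a "single-centre, randomized, unblinded feasibility trial", with no exception for outcome assessment. Under Qualitative data the article says that uptake, participation and maintenance have no suitable quantitative measure, so they are gathered by structured interview, "which will be conducted at the three and six-month follow-up points". On mode it says "Interviews will be conducted face-to-face or by telephone", and on the endpoints "The primary endpoints for the trial will be coded from this information and analyzed quantitatively". Table 2 lists uptake and adherence as qualitative, by interview, and names no other source.

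Statistical analysis defines two primary components: a yes/no acceptance of referral or self-referral, and a four-level participation scale (none, initiated, persisted, maintained). Success criteria 1 and 2, under Aims and objectives, ask for a favourable difference in referrals and participation and for favourable self-managed change. Neither carries a threshold. The Discussion makes the large trial depend on positive results and on the criteria being met.

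On the new assessment, the abstract places some intervention patients in a deferment "category, for reassessment at follow-up". Statistical analysis will explore responses to the new assessment, "including any changes between first and second assessments". Study conditions says "The assessments are delivered in the hospital ward by research staff before discharge" and describes no later delivery. Table 2 has no row for a reassessment at 3 or 6 months.

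**The concern.** The participation scale requires a judgement: someone must decide from a participant's account whether change was not begun, begun, continued or maintained. An intervention patient who mentions goal setting or a referral plan may disclose the arm in the same account. A coder who knows the arm can resolve borderline cases in its favour without intending to, and that error has a direction. Because criteria 1 and 2 have no threshold, a small spurious difference could count as success and feed the decision on a large trial.

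The second, smaller issue is timing. Deferred patients are the intervention patients held back for later reassessment. If they are reassessed at the follow-up contact before the outcome questions are asked, an acceptance made minutes earlier could be entered as uptake achieved by that time point. Controls have no equivalent contact in the text shown.

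**Working it through.** **The plan's own figure.** Sample size calculations: 120 × (1 − 0.25) = 90 patients, or 45 per arm. A two-sided 5% t test with a standardized effect of 0.6 has power 80.4% (81.2% by normal approximation), which reproduces the stated 80%. This point disputes no number in the plan.

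**Size of a coding shift.** Inputs from the article: 45 per arm and a meaningful effect of 0.4 SD. Assumed, because the article gives no uptake rate or miscoding rate: the same true uptake *p* in both arms, and a fraction *m* of intervention non-adopters coded as having initiated change, with control coding correct.

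- Spurious difference = *m* × (1 − *p*).
- 0.4 SD for a binary outcome = 0.4 × √(*p*(1 − *p*)). This conversion is mine; the article gives no binary equivalent.
- At *p* = 0.40 and *m* = 0.10: 0.10 × 0.60 = 0.06, so 46% against 40%. 0.4 × √0.24 = 0.196. Ratio 6/19.6 = 31%.

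| True uptake, both arms | *m* = 5% | *m* = 10% | *m* = 20% | 0.4 SD |
|---|---|---|---|---|
| 20% | 4.0 points | 8.0 | 16.0 | 16.0 |
| 40% | 3.0 | 6.0 | 12.0 | 19.6 |
| 50% | 2.5 | 5.0 | 10.0 | 20.0 |

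At 40% uptake the shift is 3 to 12 points, that is 3/19.6 = 15% to 12/19.6 = 61% of the meaningful difference.

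**Would the intervals show it?** For 46% against 40% with 45 per arm, the half-width is 1.96 × √((0.46 × 0.54 + 0.40 × 0.60)/45) = 1.96 × 0.104 = 20.4 points, so the interval runs from about −14 to +26. Across true uptake of 20–50% the half-width is about 17–21 points. The interval reflects sampling error around whatever was coded, so it is centred on the biased value and carries no sign of the bias. If a test were applied with no true difference, a one-arm shift of 5 points would raise the two-sided 5% rejection rate to about 8–9%, and a shift of 10 points to about 16–19%.

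**The reassessment passages side by side.**

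- Abstract: reassessment at follow-up, for the deferment category only, which is one of three intervention categories.
- Statistical analysis: a second use of the new assessment is analysed, with no statement of who receives it or when.
- Study conditions: delivery on the ward before discharge only.
- Table 2: no reassessment at either follow-up.

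The first two imply a follow-up activity that the last two do not accommodate. No passage says at which follow-up point it happens, who does it, or whether it shares a contact with the interview. Its effect on the difference cannot be sized, because the number of deferred patients is not given.

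**The case against.** The strongest reply is that this is a condensed account of an exploratory feasibility study. The article says effectiveness is not being evaluated, makes proof of concept secondary, and plans descriptive summaries with intervals. The full protocol exists and is not shown, nor is Figure 1, so who codes and from what may be set out there. The interview is structured, and yes/no acceptance of referral leaves less room for judgement than the ordinal scale. The illustrated shift rests on invented inputs and lies inside the declared uncertainty.

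Much of this stands. It limits the claim to no masking being described, puts the weight on the ordinal component, and keeps the figures as illustration. It does not remove the point: the trial is called unblinded without qualification, the endpoint has no other named source, and the decision on a large trial uses the result. A shift inside the interval still moves the estimate in one direction.

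A reader might infer more than the documents support:

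- *That the whole intervention arm is reassessed and that measurement and intervention are mixed.* The abstract names only the deferment category, and nothing puts the two in one contact or fixes their order.
- *That acceptance following reassessment is bias.* Reassessment is a planned route of the tailored strategy, and its effect is legitimately an intervention effect. Only crediting it to a time point before it occurred would be an error. Relying on 6 months alone would not change this, since acceptance prompted at 3 months would still count then.
- *That those who deliver the assessments also interview and code.* Study conditions covers ward delivery only.

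**Conclusion.** The point holds in limited form and is worth acting on. As described, the primary endpoints are coded from self-report in an unblinded trial without stated masking, and knowledge of allocation could push the coded difference towards the intervention on criteria 1 and 2. On assumed inputs (40% true uptake in both arms, 5–20% of intervention non-adopters miscoded, controls coded correctly) the push is 3–12 points against about 20 for 0.4 SD. The true size is unknown. The reassessment issue is an unreconciled description across four places, plus a conditional risk of misdated uptake that arises only if reassessment shares the contact and comes before the outcome questions. The documents do not show that this happens.

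**What to change.** 1. Have the uptake and participation categories coded against written definitions, from records carrying study ID only and with references to the assessment or plan removed. The coder should be an existing team member who does not hold the allocation and did not assess that patient.
2. At each follow-up contact, complete and lock the outcome items before any reassessment.
3. Reconcile the abstract, Study conditions, Table 2 and Statistical analysis on who is reassessed, at which follow-up, and where this falls relative to the interview.

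The cost is light redaction and a reordered interview script, with no extra visit. Some records may still reveal the arm, and masked coding does not remove any bias in what unblinded participants choose to report; the results paper should state both limits.

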#### Sample size calculations

We planned to recruit a minimum of 120 patients over four months, randomized equally between intervention and control groups. Assuming that loss to follow-up will be no greater than 25% at 6 months, this will leave 90 patients for our study. This study is designed to assess the feasibility of conducting a definitive trial; because effectiveness is not being evaluated, a formal power calculation would not usually be considered necessary for the primary objectives. However, there is a secondary proof-of-concept element to the study. Based on a two-sample Student’s *t* test with a 2-sided 5% significance level, there would be an 80% power of detecting a standardized effect size of 0.6 in any outcome variable with 90 patients at analysis. As this is larger than the clinically meaningful effect of 0.4, our results will be classed as inconclusive rather than negative if no statistically significant difference is found. We will report 95% confidence intervals and interpret the level of uncertainty based on these.

#### Statistical analysis

The primary analysis will be conducted on the intention-to-treat sample, including all randomized participants in the groups to which they were randomized. Analysis will focus on descriptive statistics and confidence interval estimation rather than formal hypothesis testing. The primary outcome of successful uptake of lifestyle advice is made up of two components: accepting referral or self-referral and participation in lifestyle interventions or self-management. The first is a binary outcome (yes, no) while the second is ordinal (none, initiated, persisted and maintained). Both will be summarized in each group, along with 95% confidence intervals to provide evidence of proof of concept.

A standard CONSORT-approved diagram will depict the flow of patients through the study from screening to analysis (see Figure 3 for enrolment to allocation stages only). This diagram summarizes the feasible eligible, recruitment and refusal rates. It will also summarize the 3- and 6-month follow-up rates. The distributions of the data at baseline, and at 3 and 6 months after randomization will be explored, with unusual values noted and explained. Baseline variables will be summarized as *n* (%), mean (standard deviation) or median (interquartile range), as appropriate, both overall and by randomized group, to characterize the sample and look for any imbalances. Risk factors for vascular events will be summarized, together with the frequency at which patients seek help. Referral choice will then be summarized by randomized group. Responses to the new assessment will be explored, including any changes between first and second assessments. Protocol violations will be reported, including an exploration of the predictors of any missing data. The primary outcomes will be summarized descriptively by behaviour change in relation to risk factors and by health-related quality of life, mood and social satisfaction to assess the relationship between the process and the clinical endpoints. Completion rates and missing item data will be summarized for key secondary outcomes, together with estimates and variances to aid calculation of sample size for a definitive trial.

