### Aims and objectives

The main aim of the study is to assess the feasibility of conducting a definitive trial in terms of recruitment, use and acceptability of the intervention, follow-up at 3 and 6 months, and data collection methods. The following criteria will be used to assess success:

1. Favourable difference shown in referrals and participation.

2. Favourable changes made through self-management.

3. Recruitment target met in time available.

4. Retention rate at 75% or more at 6 months follow-up.

5. Missing data at 10% or less, including 6 months follow-up.

6. Included participants are representative of the target population.

In addition, the study aims to establish suitable procedures for delivering the intervention and conducting assessments and procedures for ensuring recruitment and retention in the study. Finally, the study aims to discover whether using a structured, individualized approach to lifestyle assessment and referral will improve uptake and participation in lifestyle- and behaviour-change interventions;

The study will also examine, qualitatively, the acceptability of the assessment tool to patients in an acute cardiology setting as well as patients’ experiences of making lifestyle changes in order to develop effective recruitment and retention strategies.

The study will have a number of quantitative objectives:

1. To determine how many patients accept referral to a formal lifestyle programme;

2. To determine how many patients participate in a lifestyle-change intervention or initiate self-managed change;

3. To investigate the uptake of lifestyle intervention in relation to subsequent behaviour change and impact on health-related quality of life, mood and social satisfaction;

4. To estimate feasible eligibility, recruitment and refusal rates, and 3- and 6-months follow-up rates;

5. To measure key outcome domains (that is, for completion rates, missing data, estimates, variances and 95% confidence intervals for the difference between the control and intervention groups) for patients including clinical indicators and patient-reported measures of social satisfaction; health-related quality of life; and mood;

6. To synthesize data to inform the sample size of a definitive trial;

7. To determine the acceptability (and factors influencing this) of financial incentives as a method to encourage behaviour change, their pricing and factors influencing this.

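### The objective 3 summary pools self-managed change with programme participation, so its second component is linked to behaviour change partly by construction

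*Protocol article*

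**What the plan says.** The Statistical analysis section of the protocol article builds the primary outcome, successful uptake of lifestyle advice, from two components: "accepting referral or self-referral and participation in lifestyle interventions or self-management". On their scales it says: "The first is a binary outcome (yes, no) while the second is ordinal (none, initiated, persisted and maintained"). The second component does not distinguish a patient who joined a programme from one who self-managed. Objective 2, under Aims and objectives, counts patients who "participate in a lifestyle-change intervention or initiate self-managed change".

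Objective 3 is "To investigate the uptake of lifestyle intervention in relation to subsequent behaviour change", together with the impact on quality of life, mood and social satisfaction. The matching analysis is "The primary outcomes will be summarized descriptively by behaviour change in relation to risk factors" and by the three questionnaire measures, with the stated purpose "to assess the relationship between the process and the clinical endpoints".

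On data sources, the Qualitative data section says "There are no suitable quantitative measures of uptake, participation and maintenance of behaviour change", and the primary endpoints are therefore coded from structured interviews at 3 and 6 months. Table 2 lists uptake and adherence as interview items at 3 and 6 months, and smoking, alcohol, diet and physical activity as interview items at baseline, 3 and 6 months. The Assessment tools section says lifestyle change is self-reported. Quality of life, mood and social satisfaction come from posted questionnaires.

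**The concern.** A summary of process against endpoint is informative only if the two are separate events. Here, one way to score above the lowest level on the second component is to begin changing one's own behaviour. A patient who cuts down drinking unaided can appear as uptake on one axis and as changed behaviour on the other, on the strength of the same self-report. The more such patients there are, the stronger the association, whether or not referral or a programme did anything.

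What is at stake is how the objective 3 table is read. It is the planned look at whether taking up advice goes with change in risk-factor behaviour. With the two routes pooled, a reader cannot tell how much of the association is process and how much is overlap of definitions.

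**Working it through.** **The plan's own figures.** The article gives no figure for the association between uptake and behaviour. Its sample-size statement is a separate matter and reproduces: 120 × 0.75 = 90 analysed, and a two-sample t test with 45 per arm and a standardized effect of 0.6 has 80.4% power.

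**Model.** Suppose formal programmes have no effect. All inputs are assumptions, because the article gives none of them:
- p = share in a formal programme, 0.1 to 0.3
- s = share self-managing only, 0.1 to 0.4
- b = probability of reported behaviour change in programme users and in patients with neither, 0.1 or 0.3
- c = probability of reported behaviour change in self-managers, 0.7 or 1.0

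The four-level scale is collapsed to any uptake against none.

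**Formula.** Changed in the uptake group = (p·b + s·c)/(p + s). Changed in the no-uptake group = b. The difference is

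RD = [s/(p + s)] × (c − b),

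which is positive whenever self-managers report more change than the others.

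**Worked example**, p = s = 0.2, b = 0.1, c = 1:
- Uptake group: (0.02 + 0.20)/0.40 = 55% changed
- No uptake: 10% changed
- RD = 45 points; odds ratio = (0.55/0.45)/(0.10/0.90) = 11

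The plan summarizes uptake within behaviour-change groups, the same table read the other way. Uptake is 0.22/(0.22 + 0.06) = 79% among changers and 0.18/(0.18 + 0.54) = 25% among non-changers. The odds ratio is again 11.

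**Range over the grid**

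| c | RD | Odds ratio |
|---|---|---|
| 1.0 | 17 to 72 points | 2.1 to 41 |
| 0.7 | 10 to 48 points | 1.6 to 12 |

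Lowest: p = 0.3, s = 0.1, b = 0.3, c = 0.7 gives (0.1/0.4) × 0.4 = 0.10. Highest: p = 0.1, s = 0.4, b = 0.1, c = 1 gives (0.4/0.5) × 0.9 = 0.72.

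**The same data with the routes split.** Formal participants against patients with neither: b − b = 0, the assumed truth. Formal participants against everyone else is not a safe substitute, because it puts self-managers in the comparator. In the worked example the others change at (0.2 × 1 + 0.6 × 0.1)/0.8 = 32.5% against 10%, a gap of −22.5 points with no true effect.

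**What the overlap does not reach.** The first component, accepting referral or self-referral, contains no behaviour change. The questionnaire measures are separate instruments. The comparison of uptake between randomized groups does not use this table.

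**The case against.** The best defence is that no coding rule is given. The Abstract presents self-management as a guided process with goal setting, and the four levels could grade effort rather than achieved change. A patient may start or persist without altering a risk factor. Interview coding is also the kind of detail an article leaves to the full protocol. This stands in part: it is why c need not be 1 and why the size is unknown. It does not remove the overlap, since objective 2 itself words the route as initiating self-managed change and the analysis does not separate the two routes.

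A second defence is that the table is only descriptive and is not one of the six success criteria under Aims and objectives. That is correct and limits the consequence. A descriptive table is still read for its stated purpose, which is the link between process and clinical endpoints.

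A reader might also infer that the plan compares uptake and behaviour at the same visit, so that the word subsequent in objective 3 is empty. The documents do not support that. No pairing of visits is fixed, and Table 2 allows 3-month uptake to be set against 6-month behaviour.

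**Conclusion.** The point holds for the second primary component in the behaviour-change part of the objective 3 summary. As pooled, that component carries a built-in positive association with self-reported behaviour change. With zero programme effect the assumed scenarios give about 10 to 72 points. The direction requires only that self-managers report more change than the others; the size rests on shares the article does not state.

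Three stronger readings should be resisted:

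- **The link is necessarily strong.** Suppose a share f attends a programme, a proportion c of everyone changes, every unaided changer is coded as uptake, and nobody in the lowest category changes. The gap is then c/[f + (1 − f)c]: 0.30/0.44 = 68 points at f = 0.2 and c = 0.3, and 45 to 87 points over f = 0.1 to 0.3 and c = 0.2 to 0.4. The article states neither condition, and milder scenarios give odds ratios of about 1.6 to 2.
- **The whole uptake measure is circular.** Only the second component is.
- **The table would carry the case for the larger trial.** The Discussion ties progression to positive results and the success criteria, and cites an estimate with a confidence interval for the efficacy of the assessment. Nor is it a stated aim to tell a useful programme from a useless one, since the trial tests an assessment and referral tool.

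This is a contained defect in one descriptive summary, worth correcting because the correction is cheap.

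**What to change.** In the Statistical analysis section, for this summary only:

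1. Split the second component into formal programme participation, self-management only, and neither.
2. Relate referral acceptance, and formal participation against neither, as recorded by 3 months, to smoking, alcohol, diet and activity at 6 months given baseline status. This gives subsequent change a defined meaning.
3. Keep self-management in the table as its own category, since the Discussion hypothesizes that it is a route to healthy behaviour. Note that it overlaps with behaviour change by definition and that its association is not evidence of a process effect.
4. Label the table descriptive and self-selected.

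Table 2 already schedules the data, so only wording changes. The cost is smaller categories and less precision.

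One limit remains. If coding moved every unaided changer out of the neither group, that group would be depleted of changers. In the extreme illustration (f = 0.2, c = 0.3), formal participants would show 30% against 0% with no true effect. Showing all three categories with their counts lets the reader see this, and the label in step 4 should warn against reading the contrast as a programme effect.

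### For EQ-5D, CORE-10 and social satisfaction, no baseline adjustment and no baseline to follow-up correlation is stated; adding both would sharpen the estimates using data already collected

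*Protocol article*

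**What the plan says.** Table 2 of the protocol article (Visit schedule) marks EQ-5D, CORE-10 and the Social Satisfaction Questionnaire at baseline, 3 months and 6 months: "This is a longitudinal study with two follow-up points".

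The power statement (Sample size calculations) is "Based on a two-sample Student’s *t* test with a 2-sided 5% significance level" and claims "80% power of detecting a standardized effect size of 0.6 in any outcome variable with 90 patients at analysis". The same paragraph sets the clinically meaningful effect at 0.4 and classes a non-significant result as inconclusive.

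Objective 5 (Aims and objectives) covers, for the key outcome domains, estimates, variances and 95% confidence intervals for the between-group difference. Objective 6 reads "To synthesize data to inform the sample size of a definitive trial". The Statistical analysis section repeats the planning purpose for the key secondary outcomes: completion rates and missing items are summarized "together with estimates and variances to aid calculation of sample size for a definitive trial". That section has baseline variables explored and summarized, overall and by group, to describe the sample and check balance. None of these places says whether the between-group estimates are adjusted for baseline, and none lists a correlation or a residual variance among the outputs.

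**The concern.** When the same scale is measured before randomization and again at follow-up, part of the follow-up variance is predictable from the first score. A comparison of follow-up means leaves that part in the error term. Adjusting for the baseline score removes it.

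Two stated purposes of this study are affected. One is the between-group estimate with its confidence interval, which is to help decide whether a definitive trial is warranted. The other is the supply of inputs for that trial's sample size. A sample size based on a baseline-adjusted analysis needs the raw SD and the baseline to follow-up correlation (or, equivalently, the residual SD). The article names the variance but not the correlation.

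**Working it through.** **Inputs from the article (Sample size calculations).** Two-sided 5% level, 80% power, 120 recruited 1:1, 25% loss, target effect 0.6 SD, clinically meaningful effect 0.4 SD. The correlation r between baseline and follow-up is not given. It is an assumption here, shown at 0.3, 0.5 and 0.7.

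**Step 1: reproduce the stated figure.** 120 × 0.75 = 90, so 45 per arm. The two-sample t test (noncentral t) has 80.4% power at d = 0.6, and the effect detectable with exactly 80% power is 0.597 SD. The article's figure is correct for an unadjusted comparison.

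**Step 2: effect of adjustment with 45 per arm.** ANCOVA multiplies the variance of the difference by (1 − r²). All effects are in units of the raw SD, and the one degree of freedom spent on the covariate is neglected.

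- Detectable effect = 0.597 × √(1 − r²).
- 95% CI half-width = 1.96 × √(2/45) × √(1 − r²) = 0.413 × √(1 − r²) (normal approximation).

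| r (assumed) | Variance factor | Detectable effect | CI half-width |
|---|---|---|---|
| 0 (unadjusted) | 1.00 | 0.597 | 0.413 |
| 0.3 | 0.91 | 0.570 | 0.394 |
| 0.5 | 0.75 | 0.517 | 0.358 |
| 0.7 | 0.51 | 0.426 | 0.295 |

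This touches the article's own interpretation rule. With an observed difference of zero, the unadjusted interval (±0.413) still contains the meaningful effect of 0.4. At r = 0.3 the half-width is practically at that limit, and at r = 0.5 the interval excludes 0.4 clearly.

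**Step 3: illustration for a later trial.** The article computes no definitive sample size. Taking its meaningful effect of 0.4 at 80% power, n per arm = 2 × (1.96 + 0.8416)² / 0.4² × (1 − r²) = 98.1 × (1 − r²), rounded up:

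- r = 0: 99
- r = 0.3: 90
- r = 0.5: 74
- r = 0.7: 51

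A calculation that left r out would therefore ask for 99/90, 99/74 or 99/51 of the number needed: about 10%, 34% or 94% more.

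**Step 4: how well this study can estimate r.** With 90 patients and an observed r of 0.5, Fisher's z is 0.549 with standard error 1/√87 = 0.107. The 95% CI for r is therefore about 0.33 to 0.64. Put into Step 3, that interval gives 88 down to 58 per arm. The point estimate alone (74) is too uncertain to size a trial on; the lower limit (88) still improves on 99.

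**The case against.** The strongest objection is that this is silence, not a decision. The article condenses a full protocol, the analysis plan is not shown, and covariates for secondary outcomes are commonly settled there. The t test supports one generic power statement, which does not rule out an adjusted analysis. This stands. A reader might infer that the trial will ignore its baseline scores, but the article says neither adjusted nor unadjusted.

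A reader might also infer that the definitive trial's size is overstated. No such size appears in the article. The raw variance is itself an input to an ANCOVA sample size, and r can be computed later from the scheduled data. Overstatement would follow only if r were left out.

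A third tempting inference is that chance imbalance under unstratified randomization makes the unadjusted difference wrong. It does not: the difference is unbiased and its interval already allows for chance imbalance. The loss is one of precision.

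The stakes are also limited. Feasibility is the main aim. The primary outcome, uptake, is coded from interviews at 3 and 6 months and has no baseline value. The Discussion makes social functioning and emotional wellbeing secondary in the definitive trial, so CORE-10 and social satisfaction are unlikely to set its size. EQ-5D might, because health status is among that trial's targets and the article describes EQ-5D as a measure of it.

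What remains is that the article does name its planning outputs, producing them is a declared objective, and the list lacks the one further quantity that an efficient design needs.

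**Conclusion.** The point holds as a low-cost improvement, not as an error. The stated power figure is correct and an unadjusted comparison would be valid. Baseline-adjusted estimation is more precise whenever r is materially above zero. Over the assumed range of 0.3 to 0.7, the variance falls by 9% to 49% and the effect detectable with 90 patients moves from 0.60 to between 0.57 and 0.43 SD. The size rests entirely on r, which the documents do not give. If scores taken during an acute admission predict later scores poorly, the gain is at the small end. The point is confined to the three scales. It does not support saying that adjustment will be omitted, that any sample size is wrong, or that the primary outcome is affected.

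**What to change.** **Estimation.** State that, for each of the three scales, the 3- and 6-month between-group difference with its 95% CI is estimated by ANCOVA, or by one mixed model for both visits, with the baseline score as covariate. Name this in advance, so that adjustment does not depend on whether an imbalance is seen.

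**Timing.** Use baseline scores completed before randomization. The article places baseline only within the hospital admission, so the order should be confirmed.

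**Planning outputs (objectives 5 and 6).** Beside the raw SD, report the residual SD and the baseline to follow-up correlation with its 95% CI. Where one of these scales drives the definitive trial's size, use a conservative correlation such as the lower confidence limit.

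**Cost.** A few lines of analysis wording and two more columns in a table. No new data are needed, provided the baseline scores do precede randomization.
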